#### Executive functions tasks.

A key aim of this study is measuring preschool children and teacher’s EFs. Three key EF domains will be measured including cognitive flexibility, inhibition and working memory. Teacher and child EFs tasks with be delivered electronically on a touch-screen computer.

**Tasks for preschool children:** Children’s EFs will be measured using age-appropriate tasks, such as the Eight boxes and Day-Night tasks. These tasks have been developed, adapted and standardised for a Singapore population (data unpublished). Both tasks are completed on a touch screen computer and scored on their speed and accuracy.

During the *Eight boxes task*, children are presented with 2–5 fruits in different spatial arrangements in 8 boxes. After a specified time, the fruits are removed from the boxes and the child is asked to place the fruits in the previously presented arrangement. Children complete 10-trials. This task measures working memory and cognitive flexibility.

The *Day-Night task* uses similar principles as the Stroop [46] or Dimensional Change Card Sort tasks [47]. Children are taught to sort cards using one rule, then they are asked to sort cards using a second rule and finally, they were asked to sort the cards using a third rule which is a combination of rules 1 and 2. This task measures cognitive flexibility, working memory and inhibition. Although these tasks have previously been used with children of a 3–7 years, adaptations may still be required to ensure that they are appropriate for the current context.

**Tasks for teachers:** Teachers are asked to complete a longer battery of computerised EFs tasks with tasks targeting specific EF sub-domains. Selected previously established tasks are listed below:

Cognitive FlexibilityWisconsin Card sort task [48]Intra-extra-dimensional shift [49]InhibitionStop-signal [50]Stroop [46]Working memoryBackward digit span [50]Spatial working memory [49].

#### School readiness assessment.

The Brigance Early Learning Screens (III) is an assessment designed to assess children’s development from birth to 7 years [51]. The assessment samples children’s skills in a broad range of areas, including fine and gross motor, articulation, expressive and receptive language, general knowledge, personal-social skills and pre-academic skills. It is intended to be used to identify a child’s strengths and weaknesses as a form of early psychoeducational assessment, and to identify children who would benefit from additional diagnostic testing or special services. The test is scored by assigning point values to each assessed skill. Total points are compared with cut-offs with established norms. The Early Learning Screens (III) were originally normed in US populations. The test is administered by a research assistant and takes a total duration of between 15–25 minutes.

### Vocabulary assessment

The Peabody Picture Vocabulary Test is a standardised norm-referenced measure of receptive vocabulary based on Standard American English [52]. Children hear spoken words and are asked to point to the corresponding picture. A version that has been adapted and normed for a Singapore population [53] will be used.

### Teacher-child interaction tasks

#### Cooperation task.

This task was adapted from Reindl and colleagues [54]. A teacher and child will manipulate their respective on-screen animal using a keypress to catch a ball together. They will be instructed to press their keys in-time to “catch the ball together”. If the difference between the teacher and child’s key presses falls below a cut-off, the dolphins will jump together. If the difference is above the cut off, the faster respondent’s dolphin will catch the ball alone. The threshold was set to T =  1+ 1/8 (RT1 + RT2), where RT1 and RT2 are the response times of the two participants. This task will be split into 2 phases: teaching phase and test phase. During the teaching phase, the teacher and child can talk to discuss the best strategy to achieve the highest possible score, whereas the teacher and child are asked to complete the test phase in complete silence. Both phases will consist of 20 trials. In the test phase, a point will be awarded when the pair catch the ball together and a point will be deducted on trials when only one player catches the ball. The pair will start with a score of 100. Participants will be seated side-by-side facing a computer monitor with a divider between them. The divider will prevent the teacher and child looking at each other’s hands and will allow them to see the other player’s face.

#### Storybook reading task.

In this storybook reading task, the teacher and child will read a digital storybook for approximately 4 min and 30 seconds, adapted from [55]. The story, *Sally’s Space Adventure*, was designed to expose children to novel object label mappings, with objects and labels were chosen from the Novel Object and Unusual Name (NOUN) database [56]. *Sally’s Space Adventure* follows a narrative of an astronaut travelling through space to find the four novel objects needed to fix a broken rocket. All novel objects are named three times during the story: once with a colourful backdrop, once in isolation with a black backdrop, and once later in the story with an assigned function (e.g., fixing the engine of the rocket). The order and combination of novel words and novel objects will be fully randomised across participants. Teachers will not be instructed on how to engage with the child to preserve the natural dynamics of their student-teacher interactions while reading.

Children’s learning and retention of story information during the shared book reading will be assessed using a narrative recall exercise and a short quiz delivered by the teacher immediately after the story reading has finished.

#### Creative problem solving tasks.

Puzzle completion activities

Children will also be invited to participate in a series of Tangram puzzle tasks, where they will be seated next to the teacher. Children will be instructed to use a set of wooden puzzle pieces to complete a composite outlined picture on an indented board. There are a total of 4 unique puzzle task sets, separated into 4 phases. This includes a practice phase followed by 3 test phases. During the test phases only, the puzzle outlines provided to the student during the test phases include ‘shaded areas’ which require the combination of 2 or 3 separate pieces to successfully solve the puzzle. During the practice phase, the teacher will demonstrate to the student the correct way to use the provided puzzle pieces to complete the outlined picture. Supervision is provided by the teacher as needed and there is no time limit.

During each test puzzle, a new puzzle outline is provided to the student, and they are told that the puzzle contains shaded areas that may require them to do something different (compared to the non-shaded spaces). During the *first test phase*, the teacher does not provide feedback and encourages the child to complete the test as independently as possible. In the *second test phase*, the teacher actively provides verbal feedback as the child attempts to complete the puzzle. Teachers are instructed to use the teaching pedagogy with which they felt most comfortable. During the *third test phase*, children are asked to complete the puzzle independently with minimal guidance from the teacher, to assess the skills they have gained.

For each phase, the child’s completion time, and number of pieces in the correct position will be used to score their performance.

Picture Construction Activity

Children will be instructed to create a picture using the seemingly meaningless Tangram puzzle shapes. They will have 5 minutes to complete their picture. Upon completion they will be asked to describe the picture and give it a title. This task is scored on originality and elaboration (Torrance, 1964; but see Alabbasi et al., 2022).

Repeated Figures Activity

In this task, children will be asked to “build a path” to allow a character to get from one location to another. They will be presented with two squares in predefined positions attached to a laminated sheet. They will also be given 9 identical squares to use to connect those attached to the laminated sheet. Each completed solution will be reset after each response and the child was asked to try and create a new alternative solution. Feedback will be provided if their path isn’t compliant with the rules of the task. Children will have 4 minutes to play this game and the time taken to reset the pieces between solutions doesn’t contribute to the time. This activity was designed to elicit the tendency to repeatedly return to the same stimulus and perceive it in new ways. Scoring for this activity focused on fluency, and originality (Cramond, 1994).

### Neurophysiological measures

Whilst performing the teacher-child interaction tasks including the cooperation task, storybook reading task and creative problem tasks, as well as the EFs tasks, teachers and children will be asked to undergo concurrent EEG and ECG recordings. The EEG will be recorded using 32-channel system in a standard international 10/20 configuration. Event triggers will be sent to the EEG amplifiers to ensure synchronisation with task stimuli.

### Questionnaire measures

We will also administer teacher and caregiver self-report questionnaires, as well as caregiver-report questionnaires covering temperament, child behavior, parenting and family background information, such as their home language environment, parental education, household income etc.

#### Teacher-student relationship ratings.

The student- and teacher-report versions of the *Teacher-Student Relationship Inventory (S- & T-TRSI; 55)* will be used as a culturally adapted instrument to measure children’s and teacher’s subjective rating of each other. The TSRI (student and teacher versions) measure three factors: satisfaction, instrumental help, and conflict using a simple pictorial Likert scale. The psychometric properties of the TSRI have been validated for use in Singaporean populations using data from the Singapore Ministry of Education, showing reliability and validity across different genders, grade levels, and academic performance groups [57,58]. This student version of the questionnaire has been adapted for the slightly younger age of the children in this study. The student version will be administered by an experimenter to account for differences in reading ability.

#### Parent and teacher self-report questionnaires.

*Behavior Rating Inventory of Executive Function–Adult Version* (BRIEF-A) [59]: Self-report questionnaire designed to evaluate executive functions in adults aged 18–90 years, covering aspects such as inhibitory control, shifting, task monitoring, emotional control, and working memory.

*Adult Temperament Questionnaire* (ATQ) [60]: Self-report questionnaire designed to measure temperament traits in adults, focusing on dimensions such as effortful control, negative affect, extraversion, and orienting sensitivity.

*Perceived Stress Scale* (PSS) [61]: Self-report questionnaire that measures the perception of stress, evaluating how unpredictable, uncontrollable, and overwhelming respondents find their lives.

*State-Trait Anxiety Inventory* (STAI) [62]: Self-report measure that assesses both state anxiety (temporary condition) and trait anxiety (general tendency), providing insights into anxiety levels in individuals.

*Beck Depression Inventory* (BDI) [63]: Self-report questionnaire used to assess the severity of depression symptoms in individuals, covering emotional, cognitive, and physical aspects.

#### Parental questionnaires completed on behalf of their child.

*Behavior Rating Inventory of Executive Function – Preschool* (BRIEF-P) [64] or *The Behavior Rating Inventory of Executive Function* (BRIEF) [65] are parental report questionnaires designed to evaluate executive functions in children aged 2–5 and 5–18 years respectively. These assessments cover areas such as inhibition, working memory, and emotional control.

*Early Childhood Behavior Questionnaire* (ECBQ) [66] or *Childhood Behavior Questionnaire* (CBQ) [67,68]: Parent-report measures that assesses temperament in children aged 1.3–3 and 3–7 years respectively, focusing on dimensions like emotional reactivity, self-regulation, and sociability.

*Child Behavior Checklist* (CBCL) – versions for 1.5–5 and 6–18 years [69,70]: A widely used parent-report questionnaire that evaluates behavioral and emotional problems in children, covering areas like anxiety, depression, aggression, and social problems.

*Language Exposure Assessment Tool* (LEAT) [71]: A parent-report tool designed to assess the amount and type of language exposure a child receives, particularly in bilingual or multilingual contexts.

*Children’s Sleep Habits Questionnaire* – short form (CSHQ-sf) [72]: Parent-report questionnaire that evaluates sleep behaviors and problems in children aged 2–10 years, covering domains such as bedtime resistance, sleep duration, and night wakings.

*Alabama Parenting Questionnaire* – Preschool Revision (APQ-PR) [73] or *Alabama Parenting Questionnaire* (APQ) [74]: Parent-report measures that assesses parenting practices in children 2–6 and 6–18 years respectively, focusing on aspects like involvement, positive discipline, and inconsistent discipline.

*Family Interview for Genetic Studies* (FIGS) [75]: a series of questions design to obtain a comprehensive family history information on psychiatric disorders, medical conditions, and social functioning to aid in genetic research.

### Analysis plan

A combination of standard regression and machine learning methods will be used to identify characteristics of teacher-child social interactions that significantly predict EFs and school readiness scores (Research Question 1). Examples of behavioural indices of interaction quality are ostensive signals (gaze, speech, gestures), number of teacher prompts used, difficulty level of teacher prompts, number of prompts responded to by the child and complexity of child response. These behavioural indices of interaction quality along with individual teacher and child characteristics, such as personality or temperament, will be used to as factors to predict child EFs and school readiness. Data reduction methods such as least partial squares or principal components analysis may be used to reduce the dimensionality of data and prevent multicollinearity issues. These reduced factors will be used to predict school readiness and EFs.

To explore which characteristics of teacher-child neural coupling are associated with successful teacher-child interactions (Research Question 2) indices of neural coupling will be calculated from the dyadic EEG data and will be analysed in relation to learning outcomes on scaffolding tasks, as well as the behavioural indices of interaction quality that explain the most variance in EFs and school readiness. Examples of indices of neural coupling are weighted phase lag index (wPLI) or partial directed coherence (PDC). wPLI is a non-directional measure of neural coupling which will describe linear dependencies between the phase neural oscillations between two channels. This may be used to measure connectivity within the teacher or child’s brain, as well as between the teacher and child’s brains. PDC, alternatively, is a directed measure of connectivity and will provide additional information about the directionality of the flow of information. We will also explore the extent to which synchrony in the participants ECG is associated with successful teacher-child interactions.

For data-driven analyses, the combination of dyadic EEG and behavioural interaction data will be used to create multimodal AI models to phenotype children who are at risk of poorer school readiness outcomes. Specifically, we intend to utilise models such as cumulative link [76] and ordinal temporal deep learning models [77] to predict school readiness and executive functions. The use of neurophysiological recordings alone, as well as a combination of both neurophysiology and behavioural data mentioned in previous sections will be explored. Such models will be trained using mean squared error and likelihood-based objective functions to ensure best model fit [78]. The use of such models would also allow latent state analysis since both these models effectively learn low-dimensional features from high-dimensional neurophysiological and behavioural data relevant to executive functions and school readiness leading to mechanistic insights.

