EFs are a constellation of partially dissociable higher-order cognitive processes that allow goal-directed behaviour. Significant development of EFs occurs between the ages of 3 and 5 years [18], which is the age which many children attend preschool. EFs play a significant role in the ability to regulate attention, emotion and behaviour in preschool children, which are essential for successful engagement in the classroom [19]. EFs provide a foundation for academic achievement and school performance by contributing to the children’s social functioning, emotion regulation and intentional learning [20]. This is exemplified by evidence that EFs are associated with children’s academic trajectories [13,21,22]. Cameron and colleagues report evidence for co-development of EFs and academic skills with improvements in EFs being associated with improvements in applied problem solving in 5 year old children, EF sub-domains were not assessed separately in this investigation [21]. Furthermore, EFs have long-term effects impacting several domains including academic success, impulse control, constraint and emotion regulation [23]. Previous intervention research indicates that EFs can be malleable and training of EFs has been linked to early academic success [13,24,25]. This highlights the critical role of EFs in school readiness and wider child development, as well as the importance of identifying factors that support development of EFs and the mechanisms by which this development occurs.

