### The current investigation

This study will assess the relationship between teacher-child neural synchrony, child development of EFs and school readiness in preschool-age children. Children will be assessed cross-sectionally between the ages of 2 and 7 years. Children will complete EFs, vocabulary and school readiness assessments. Additionally, children and teachers will take part in interactive tasks whilst undergoing dyadic electroencephalography (EEG) and electrocardiogram (ECG) recordings to assess teacher-child interpersonal neural synchrony.

Study objectives and research questions:

Which teacher-child behavioural interaction characteristics are associated with individual differences in preschool children’s executive function and school readiness?Does teacher-child neural synchrony during scaffolded tasks predict learning outcomes, including executive function and school readiness?

Explorative analyses:

Do different forms of teacher scaffolding (e.g., patterns of multimodal ostensive signals or dialogic reading framework) relate differentially to behavioural or neural synchrony?How do teacher individual characteristics (e.g., EF, stress, temperament) moderate the relationship between scaffolding and child outcomes?

The study protocol will be described in eight main sections: study preparation, EFs tasks, school readiness assessment, vocabulary assessment, teacher-child interaction tasks, creative problem solving tasks, neurophysiological measures and questionnaire measures.

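### Two of the five example interaction-quality indices are the child's own verbal performance, so existing child ability can pass as interaction quality when school readiness is the outcome

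*Protocol article*

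**What the plan says.** Research Question 1 (The current investigation) asks: "Which teacher-child behavioural interaction characteristics are associated with individual differences in preschool" children's executive function (EF) and school readiness. The same section states the design: "Children will be assessed cross-sectionally between the ages of 2 and 7 years". Under Recruitment overview, the teachers and children are unacquainted beforehand.

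The Analysis plan offers five examples of behavioural indices of interaction quality. Three are ostensive signals, the number of teacher prompts and the difficulty of those prompts. The other two are the "number of prompts responded to by the child and complexity of child response". A separate group of predictors is entered with them: "along with individual teacher and child characteristics, such as personality or temperament, will be used to as factors to predict child EFs" and school readiness. Partial least squares or principal components may be used to reduce the predictors.

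For Research Question 2, neural coupling is related to two things: learning outcomes on the scaffolding tasks, and whichever interaction indices account for most of the variance in EF and readiness.

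The readiness outcome is the Brigance screen. Besides motor skills, its content includes "articulation, expressive and receptive language, general knowledge, personal-social skills and pre-academic skills" (School readiness assessment). Child vocabulary is measured with the Peabody test (PPVT), a "standardised norm-referenced measure of receptive vocabulary" (Vocabulary assessment).

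**The concern.** How many prompts a child answers, and how complex the answers are, depends on the child's language. So does part of the Brigance score. A child with stronger language will tend to do better on both, whatever the teacher does. The count of prompts answered is also capped by the number of prompts given, so it mixes the two partners.

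The design cannot separate these explanations. Readiness is measured once, and a teacher met for the study cannot have produced the readiness the child brings to it.

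Three consequences follow.

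- The child-side indices may rank high in Research Question 1 because they partly re-measure the outcome.
- If components pool child output with teacher behaviour, the two can no longer be told apart.
- Selecting by variance explained tends to pass the overlapping indices into Research Question 2, where neural coupling would be related in part to child language.

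This matters because Significance and impact looks to the results for measures of teaching quality and for an account of how interaction supports EF development.

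**Working it through.** **The plan's own figure.** Sample size gives R² = 0.09, 12 predictors, 80% power and 5% type 1 error.

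- f² = 0.09 / (1 − 0.09) = 0.0989.
- The overall F test with 12 and n − 13 degrees of freedom and noncentrality f² × n reaches 80% at n = 187 (power 0.803).
- 187 × 1.10 = 205.7, so 206.

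The stated sample size reproduces and is not in question. It matters here only because 9% is the scale on which the study expects to see effects.

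**R² from child language alone.** The documents give no correlations, so all of these are assumed. Let a be the correlation of child language with response complexity (0.4 to 0.6) and b its correlation with the Brigance (0.5 to 0.7). Let the teacher have no effect. The implied correlation between complexity and the Brigance is a × b, and R² is its square.

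| a | b | r = a × b | R² | Power for this one predictor, n = 187 |
|---|---|---|---|---|
| 0.4 | 0.5 | 0.20 | 0.040 | 0.79 |
| 0.5 | 0.6 | 0.30 | 0.090 | 0.99 |
| 0.6 | 0.7 | 0.42 | 0.176 | 1.00 |

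**Effect of adjusting for vocabulary.** Take a = 0.5 and b = 0.6, and let the PPVT correlate c with child language. Then r(complexity, PPVT) = 0.5c and r(Brigance, PPVT) = 0.6c.

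- c = 0.8: partial r = (0.30 − 0.40 × 0.48) / √[(1 − 0.16)(1 − 0.2304)] = 0.108 / 0.804 = 0.134, so partial r² = 0.018.
- c = 0.7: partial r = (0.30 − 0.35 × 0.42) / √[(1 − 0.1225)(1 − 0.1764)] = 0.153 / 0.850 = 0.180, so partial r² = 0.032.

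**Simulation with no interaction effect.** There were 1,000 runs per setting, with n = 187 and 12 predictors. Two predictors were child-response indices loading on child ability, and the outcome loaded 0.6 on ability. The table gives the share of runs in which at least one of the two indices was significant at 0.05.

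| Loading of the two indices | No ability covariate | Covariate loading 0.7 | Covariate loading 0.9 |
|---|---|---|---|
| 0 | 9% | 9% | 9% |
| 0.3 | 87% | 46% | 18% |
| 0.5 | 99.7% | 83% | 27% |

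Without a covariate, mean adjusted R² was 0.06 at loading 0.3 and 0.14 at loading 0.5. An imperfect ability covariate reduces the problem but does not remove it, so the two kinds of index need to be separated as well as adjusted.

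**The case against.** Research Question 1 is worded as association and concerns the dyad. A child's uptake of prompts is a fair part of an interaction, and Limitations and future directions concedes that scaffolding is not manipulated. This stands as a defence of measuring the child's responses. It does not justify reading them together with teacher behaviour as one quality.

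Language is one Brigance area among several, and the child EF tasks are touch-screen tasks scored on speed and accuracy. This stands too: the overlap concerns mainly readiness, not EF.

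The indices are only examples, and a fuller analysis plan may name covariates. A reader might infer that the PPVT has been left out of the analysis. A condensed article does not support that inference, and the point does not rest on it. It rests on the label the article does give to the two child-side indices and on the selection rule it does state.

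The magnitude is illustrative. The 9% result comes from the middle of the assumed ranges, and it sets the R² of one predictor beside the overall R² for 12. It shows scale and is not an estimate.

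The teacher-side set is not free of child influence either. Teacher scaffolding and interpersonal synchrony says that teachers reduce support as the child's skill grows. This limits the remedy without removing the reason for it.

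**Conclusion.** The concern holds for school readiness. As written, the plan lets the child's existing verbal ability appear as interaction quality, and the Research Question 2 selection rule favours the affected indices. Under the assumed correlations and no teacher effect, response complexity alone would show an R² of about 4% to 18%. The actual size cannot be known from the documents. Research Question 2's other target, learning outcomes on the scaffolding tasks, does not depend on the selection.

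Three stronger readings are not supported.

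- A reader might infer that parent-rated temperament is also counted as interaction quality. The temperament scales are described as "focusing on dimensions like emotional reactivity, self-regulation, and sociability", and School readiness and executive functions says "EFs play a significant role in the ability to regulate attention, emotion and behaviour in preschool children". But the Analysis plan lists temperament among individual characteristics, separate from the interaction indices. It could be mistaken for interaction only if the groups were pooled or total R² were credited to interaction.
- Nor does it follow that self-regulation scales must be dropped when EF is the outcome. The kinship is of construct, not of items or method, and entered separately such a scale may serve as partial adjustment.
- A reader might infer that the study would report effects with no teacher contribution. That is true only under the illustration's own assumption of no teacher effect.

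**What to change.** Revise the Analysis plan as follows.

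1. Define a teacher-side set (ostensive signals, number of prompts, prompt difficulty) and a child-side set (prompts answered as a proportion of prompts given, response complexity). State that ostensive signals are coded from the teacher, in line with the exploratory question that treats them as a form of scaffolding.
2. Do not pool the two sets, or child characteristics, in the same principal components or partial least squares factors.
3. For Research Question 1, report the incremental R² of the teacher-side set over child age and the child-side measures. Add a sensitivity analysis that includes the PPVT score.
4. For Research Question 2, select indices within the teacher-side set, or separately within each set.

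The cost is wording and some extra reporting, since all the variables are already planned. The variance credited to interaction will be smaller. The PPVT may over-adjust because it overlaps the receptive language in the Brigance, which is why it belongs in a sensitivity analysis. Teacher prompts may adapt to the child, so the teacher-side result will be cleaner but should still not be read as a pure teacher effect.

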#### Sample size.

Research question 1 will be addressed using regression methods; therefore, a power calculation has been performed using RStudio (version 2024.04.1 + 748, Posit Software) and pwr library (version 1.30) to obtain an *R*_*2*_ value of 0.09, which is roughly equivalent to a medium effect as Cohen’s *d*. A sample of 187 children would permit the explanation of 9% of the variance with 12 predictor variables, 80% power and 5% chance of type 1 error. To account for attrition an additional 10% will be recruited to give a final sample size of 206 children. Up to 50 preschool teachers will be recruited, but fewer teachers may be required if they elect to take part with several children.

Children and teachers will be eligible if they do not have any identified genetic, metabolic, syndromic, or progressive neurological disorder, (e.g., epilepsy, Down or Rett Syndrome, Autism Spectrum Conditions, Attention Deficit Hyperactivity Disorder, Tuberous Sclerosis, Neurofibromatosis, Fragile X Syndrome,).

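### Partial least squares and PCA are offered as interchangeable reductions before a significance-based prediction of EF and school readiness; if PLS is chosen and tested by ordinary regression in the same children, the 5% level is lost

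*Protocol article*

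**What the plan says.** The Analysis plan section of the protocol article sets the aim for Research Question 1: to "identify characteristics of teacher-child social interactions that significantly predict EFs and school readiness scores (Research Question 1"). On method it says "A combination of standard regression and machine learning methods will be used". It then turns to the number and collinearity of the candidate predictors: "Data reduction methods such as least partial squares or principal components analysis may be used to reduce the dimensionality of data". The next sentence reads "These reduced factors will be used to predict school readiness and EFs". I take the first-named method to be partial least squares, with the words transposed.

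The Sample size section plans one sample, 187 children before attrition, for an R² of 0.09. It gives the conditions of that calculation, including the error rate, as "with 12 predictor variables, 80% power and 5% chance of type 1 error". No second sample is described.

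**The concern.** The text joins the two methods with a plain *or* and gives them the same next step: reduce, then predict EF and readiness. That sequence is sound for PCA, whose components depend only on the predictors. It is not sound for PLS with ordinary p-values, because PLS weights each predictor by its covariance with the outcome. Testing the resulting component against the same outcome in the same children counts the chance covariance twice: once to build the component and once to test it.

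What is at stake is the main inferential claim of Research Question 1. Of the two named routes, one keeps the stated 5% type 1 error and the other does not unless its inference is handled differently. Nothing in the text separates them, and the optional wording leaves the choice open until data are in hand.

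**Working it through.** **The plan's own figure.** For the overall F test, u = 12 predictors, R² = 0.09 and f² = 0.09/(1 − 0.09) = 0.0989. With n = 187, v = 187 − 12 − 1 = 174 and λ = 0.0989 × 187 = 18.5, which gives power 0.803; n = 186 gives 0.7999. So 187 is reproduced, and 187 × 1.10 = 205.7 rounds to the stated 206. This figure is not in dispute. It is the source of the n, the 12 and the 5% used below.

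**Inputs to the check.**
- n = 187, α = 0.05 and 12 predictors: Sample size section.
- 7 predictors: a count of the example behavioural indices in the Analysis plan (gaze, speech, gestures, number of prompts, difficulty of prompts, prompts responded to, complexity of response).
- 14 and 20 predictors: assumptions. The article does not say how many variables enter the reduction.
- Common pairwise correlation ρ of 0, 0.3, 0.6 or 0.8: assumption. Collinearity is the article's own reason for reducing, so the higher values matter.
- The outcome is independent of every predictor, so every rejection is false.

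**Formulas.** With X standardised and y centred, the first PLS component is t = Xw with w = X′y. For PCA, w is the leading eigenvector of X′X, which does not involve y. In both cases R² = (t′y)²/[(t′t)(y′y)] and F = R²/[(1 − R²)/185], referred to F(1, 185).

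**Result: rejection rate of the nominal 5% test on noise, one component, 4,000 simulations per cell.**

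| Predictors | ρ = 0 | ρ = 0.3 | ρ = 0.6 | ρ = 0.8 | PCA, all ρ |
|---|---|---|---|---|---|
| 7 | 80% | 64% | 27% | 12% | about 5% |
| 12 | 99% | 89% | 36% | 13–14% | about 5% |
| 14 | about 100% | 93% | 39% | 15% | about 5% |
| 20 | 100% | 98% | 41% | 16% | about 5% |

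Separate runs agreed to within a few percentage points.

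**More than one component.** Correlation protects only the one-component case. With three PLS components and 12 variables, rejection is 81% to 82% whether ρ is 0, 0.3 or 0.6 (2,000 simulations per cell).

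**Does the remedy restore the level?** With weights built in one half of the children and tested in the other, one PLS component rejects in 4.5% to 5.4% of runs (12, 20 or 40 variables, ρ 0 to 0.6). When the outcome is permuted and the component rebuilt each time (12 predictors, 199 permutations, 1,000 simulations), rejection is 4.9% at ρ = 0 and 5.0% at ρ = 0.6. The fault lies in the ordinary test, not in PLS as such.

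**The case against.** The strongest reply is that the fault is inferred. The methods are introduced with *such as* and *may*. The text never says that PLS components enter an ordinary regression, or that they are tested in the children who built them. Predicting an outcome from its components is what PLS regression does, machine learning is named alongside regression, and fold structure or permutation schemes are commonly left to a fuller plan that is not shown. This stands as a limit: the inflation is conditional on choosing PLS and testing it naively, and the absence of validation detail is not itself the finding. It does not remove the point, which rests on something the article does state: an outcome-driven and an outcome-blind method are offered as equivalents before a significance-based step, with one sample described.

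It can also be said that independent predictors are the least relevant case when reduction is motivated by collinearity. That is right, and it is why the range starts at about 12%. Even there the rate is more than twice nominal.

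Three stronger readings are tempting and are not supported.

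- **Research Question 2 is circular in the same way**, because neural coupling is related to learning outcomes "as well as the behavioural indices of interaction quality that explain the most variance in EFs and school readiness". Here the selection is on EF and readiness, but the test is against neural coupling, a different variable. Simulation with 187 children and the best of 7 null indices gives about 5% false positives if coupling is unrelated to EF. The rate is roughly 8% to 12% if coupling truly correlates 0.3 to 0.5 with EF. That is mild and conditional.
- **The AI models will be judged on their training data**, because "Such models will be trained using mean squared error and likelihood-based objective functions to ensure best model fit". That sentence names a training loss; it is not a rule for evaluating performance.
- **Noise alone would reach the 9% target.** Null in-sample R² for one PLS component averages 7.1% with 14 independent predictors and 9.8% with 20. Ordinary regression gives p/(n − 1), which is 14/186 = 7.5% and 20/186 = 10.8%. The 9% is a population effect in a power calculation whose F test already allows for this.

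**Conclusion.** The point holds in conditional form. The Analysis plan treats PLS and PCA as interchangeable, and for significance testing they are not. If PLS is used and its components are tested by ordinary regression in the same children, the stated 5% error becomes about 12% to 100% over the assumed range, and about 14% to 99% at 12 predictors, against about 5% for PCA. These figures assume n = 187, one component, 7 to 20 equally correlated predictors (ρ from 0 to 0.8) and no true effect. The article fixes neither the number nor the correlation of the variables, so no single value can be given. A reader might infer that the plan commits to testing components on the data that built them. It does not say so; that is one permitted reading of an optional step. The matter should be settled before analysis. It does not affect the sample size figure, Research Question 2 or the AI models.

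**What to change.** State in the Analysis plan that, for the Research Question 1 regression inference, predictors will be reduced by PCA or another method fitted without EF or readiness.

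If PLS is kept, state three things:
- Components are built inside cross-validation that holds out whole teachers. Up to 50 teachers serve about 200 children, so one teacher's characteristics can recur across several children and should not sit in both the training and the test folds.
- The reported R² is the out-of-fold value.
- The p-value comes from permuting the outcome and repeating the whole pipeline, including component building and any choice of the number of components.

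The cost is a few sentences of analysis wording, some computing time and a lower reported R². Recruitment and data collection, which the article plans into 2027, are unaffected.
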